#### Digital and Health Literacy

Digital health literacy will be evaluated using the generic Health Literacy Survey-19 Digital Health Care in Norwegian (HLS19-DHC-NO). It measures the skills in using electronic tools to follow-up on one’s own health and disease, as well as the competence to use digital home-based follow-up. This scale contains 10 items that are scored on a 4-point Likert scale from very hard to very easy, in addition to an “I don’t know” category. It has recently been translated and applied to a Norwegian population survey [45] and is currently under validation.

The 12-Item Short-Form Health Literacy Survey Questionnaire is a generic measure of the ability to make informed health choices through 4 domains: access, understand, appraise, and apply health information. This scale contains 12 items, which are scored on a 4-point Likert scale that ranges from “very hard” to “very easy,” in addition to an “I don’t know” category. The 12-Item Short-Form Health Literacy Survey Questionnaire has been validated among the general Norwegian population [46].

#### Patient Acceptability of Digital Care

To assess the patients’ satisfaction and acceptability with participating in digital care, we will use the Service User Technology Acceptability Questionnaire, which has 22 items [21]. The Service User Technology Acceptability Questionnaire measures the acceptance of mobile health technology and can also be used to identify the characteristics of participants with low acceptance of technology. The responses are given on a 6-point Likert scale, ranging from strongly agree to strongly disagree. It has been translated into Norwegian and validated in a previous study [47].

#### Sociodemographic and Clinical Variables

Sociodemographic variables will be extracted from the patient records, whereas clinical variables will comprise self-reported data and data extracted from the patients’ medical records (Table 2).

**Table 2 table2:** Sociodemographic and clinical variables.

Variables, scale, and interpretation				Time point		
				T0		T1
**Sociodemographic variables**						
	**Age**					
		Years	✓			
	**Sex**					
		Female or male	✓			
	**Education**					
		Not completed primary school (10 years) Primary upper secondary school Vocational school College or university (≤4 years) College or university (>4 years) Unknown	✓			
	**Employment status**					
		Employed 100% Student Unemployed (disability benefits or retired or other) Part-time employment (≤25%, 26%-50%, 51%-75%, 76%-99%)	✓		✓	
	**Cohabitation status**					
		Living alone yes or no	✓			
	**Ethnicity**					
		European Asian African Unknown	✓			
	**Tobacco habits**					
		Current user Previous user	✓		✓	
**Clinical variables**						
	**Diabetes duration**					
		Years	✓			
	**HbA_1c_^a^**					
		Mmol/mol	✓		✓	
	**Time in the range**					
		The last 14 days Time below range <3.9 mmol/L Time in range of 3.9-10 mmol/L Time above range >10 mmol/L	✓		✓	
	**Diabetes complications**					
		Number of diabetes late complications; Albuminuria, treated with dialysis, transplanted kidney, retinopathy, neuropathy, stroke, arterial vascular surgery, amputation, and diabetic foot ulcers	✓			
	**Equipment**					
		Pump, CGM^b^ sensor, pump and pen	✓		✓	
	**DKA^c^**					
		Never Once Several times Unknown	✓		✓	
	**Hypoglycemia in need of help**					
		Never Once Several times Unknown	✓		✓	
	**Symptomatic hypoglycemia**					
		Number of incidents, 0-90 past 30 days	✓		✓	
	**Height**					
		cm	✓			
	**Weight**					
		kg	✓		✓	
	**Lipid status**					
		LDL^d^-cholesterol, mmol/L	✓		✓	
	**Blood pressure**					
		Systolic and diastolic mm Hg	✓		✓	
**Comorbidity**						
	**CCI^e^**					
		Myocardial infarction, congestive heart failure, peripheral vascular disease, cerebrovascular accident or transient ischemic attack, dementia, chronic obstructive pulmonary disease, connective tissue disease, peptic ulcer disease, liver disease, hemiplegia, chronic kidney disease, solid tumor, leukemia, lymphoma, and AIDS	✓			

^a^HbA_1c_: glycated hemoglobin.

^b^CGM: continuous glucose monitoring system.

^c^DKA: diabetic ketoacidosis.

^d^LDL: low-density lipoprotein.

^e^CCI: Charlson Comorbidity Index.

#### Utilization of Health Care Resources

Data regarding the utilization of health care resources will be collected, including the type of health care services provided, frequency of utilization, participation, and any engagement in digital services. The variables are presented in Table 3.

**Table 3 table3:** Utilization of digital solutions and health care resources.

Variables, scale, and interpretation				Time point		
				T0		T1
**Health care use**						
	**Consultation type**					
		Physical, video, or telephone			✓	
	**Attendance**					
		Number of on-attendance and number of late cancelations			✓	
	**Health care profession**					
		Number of consultations with a physician, a nurse, and a nutritionist			✓	

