### Aims

The overall aim of this protocol is to describe our prospective multimethod observational study designed to investigate digital PROMs in a routine specialist outpatient setting for flexible patient-centered diabetes care. Specifically, the DigiDiaS will (1) quantitatively investigate and describe the characteristics of patients with type 1 diabetes participating in a digital PROM in comparison with patients in traditional follow-up and evaluate the effect of participating in digital PROMs on clinical outcomes, self-management, diabetes distress, quality of life, and health care utilization and (2) qualitatively, through observations and qualitative interviews, assess patients’ acceptability of consultations prepared and supported by digital and flexible services using PROMs.

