### Overview of the Implemented Service

#### A Digital and Flexible Service

All patients at the clinic will be offered to engage with digital and flexible services in addition to standard care. If they are interested, the digital service will be available through a mobile app on their private smartphone and will contain functions for self-monitoring, chat, video consultations, and PROMs before or between consultations. The digital PROMs implemented in this study have been described in detail elsewhere [25]. Standard care at the outpatient clinic includes a once-a-year consultation with an endocrinologist, a diabetes specialist nurse, or both. In the given situations, patients have ≥1 added consultation a year [29]. The clinic offers video-based and physical face-to-face consultations based on the patient’s preferences and needs for care through solutions approved by the hospital.

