### Study Outcomes

#### Overview

The primary outcome in this study is the change in self-management, as measured through the Patient Activation Measure (PAM) questionnaire after 1 year, which will then be compared between the users and the nonusers of the digital PROM. The secondary outcomes include glycated hemoglobin (HbA_1c_), quality of life, health literacy, acceptability, health economics, and the use of health service resources. Quantitative data will be collected through patients’ self-reports and the extraction of clinical variables from patients’ medical records. In addition, data on the patients’ use of MyDignio will be extracted, including how many clinical PROMs they completed during the study period. Self-reported and clinical variables will be collected among all consenting participants, regardless of their participation in the digital solution. The standardized self-reported outcome measures are presented in Table 1.

**Table 1 table1:** Standardized self-reported outcome measures.

Domain and questionnaire and item, scale, and interpretation					Time point						
					T0		T1				

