	**GP^a^ visits**					
		Number of GP consultations			✓	

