	**Absence from work**					
		Days of absence			✓	

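### Health care use is scheduled at T1 only, so a utilization or cost difference between the self-selected groups mixes prior differences in use with any effect of the digital PROM

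*Protocol article*

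**What the plan says.** The Aims section of the protocol article states that the study will "evaluate the effect of participating in digital PROMs on clinical outcomes, self-management, diabetes distress, quality of life, and health care utilization". The Overview under Study Outcomes lists among the secondary outcomes "acceptability, health economics, and the use of health service resources".

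Table 3 sets out what is collected and when. Five rows stand under health care use, and each is ticked at T1 only:

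- which professionals were seen, and how often: "Number of consultations with a physician, a nurse, and a nutritionist"
- time off the job: "Days of absence"
- the form that a contact took: "Physical, video, or telephone"
- primary care contacts: "Number of GP consultations"
- how reliably appointments were kept: "Number of on-attendance and number of late cancelations"

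In the same table, patient involvement, participation in digital care (with its start date) and use of other health apps are ticked at both T0 and T1.

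The Sample Size section says that patients choose their group and that the choosers can be assumed to differ from those who stay with traditional care. The Statistical Analysis section names age, gender and education as the variables for confounder adjustment. The Health Economy section compares users with standard follow-up. It takes EQ-5D-5L at baseline and 12 months and draws resource use from survey data. The Procedures section says that a researcher extracts data from each patient's medical record, with a second researcher checking 10%.

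**The concern.** In a randomized trial, a count of visits over follow-up is enough to estimate an effect on visits, because the groups start alike in expectation. Here the patients choose, and the protocol expects the choosers to differ. If users and nonusers already attended the clinic at different rates, that difference reappears in the follow-up year whether or not the digital PROM does anything. No measure of earlier use is scheduled, so it cannot be put into a model or even tabulated.

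Two results depend on this: the utilization part of aim 1, and the cost side of the cost-utility analysis. In the latter, the health benefit can be adjusted for its baseline and the resource use cannot.

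**Working it through.** The plan gives no figure for utilization, so there is none to reproduce. The check is a short derivation, an illustration on assumed inputs, and a look at the dates.

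**1. What a T1 comparison estimates.** Let m be the mean follow-up use of nonusers, g the difference in use that would exist between the groups without the service, and e the effect of the service.

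- Users at T1: m + g + e
- Nonusers at T1: m
- Difference: D = g + e

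This is one observed quantity with two unknowns. Adjusting for age, gender and education replaces g by the part of g that those three variables do not explain. It removes g only if they explain all of it.

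**2. Cost.** With unit cost c for each type of contact, incremental cost is the sum of c × (g + e) over contact types, so g enters in full. Probabilistic sensitivity analysis covers parameter uncertainty. It does not separate g from e.

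**3. Illustration of size.** From the Results section: 186 users and 34 nonusers enrolled by September 6, 2023. Assumed, not in the documents: SD 1.5 visits a year, e = 0, a stable g of 0.5 or 1.0 visits a year, and a year-to-year correlation r of 0.3 to 0.7.

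- Standard error of D = 1.5 × √(1/186 + 1/34) = 1.5 × 0.1865 = 0.280
- g = 0.5: 0.5/0.280 = 1.79 standard errors
- g = 1.0: 1.0/0.280 = 3.57 standard errors

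Simulation with 3,000 runs per setting:

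| Assumed gap | T1-only estimate (size) | T1-only false positives | Change-score estimate | Change-score false positives |
|---|---|---|---|---|
| 0.5 | 0.5 | 42–44% | about 0 | about 5% |
| 1.0 | 1.0 | 94–95% | about 0 | 4–5% |

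The simulation gave users the lower use; that sign is arbitrary. The change score is unbiased here by construction, because the gap was made stable. The table shows the mechanism. It does not show that a gap exists.

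**4. What covariate adjustment would recover.** In the same linear set-up, adjusting for one prior-year count has slope r and leaves g × (1 − r). For g = 0.5 this is 0.5 × 0.7 = 0.35 at r = 0.3 and 0.5 × 0.3 = 0.15 at r = 0.7. Adjustment reduces such a gap but does not remove it.

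**5. Which earlier period is clean.** The Results section puts the start of the service in November 2021 and the first completed T0 on October 27, 2022, about 11 months later. A user who started at launch could have most of the 12 months before T0 already exposed. T0 is therefore not a pre-exposure point for every user. Table 3 does record the start date of digital participation.

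**The case against.** **Counts over a period are normally collected at its end.** This is fair: the Table 3 rows for PROMs completed and messaging are also counts ticked at T1 only. A tick shows when data are collected, not the window covered, and a condensed article may leave the window to a fuller document. So T1 collection is no fault for describing or costing use. But nothing in the schedule assigns a count before exposure, and an analysis plan cannot adjust for data that are not collected.

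**The protocol discloses the problem.** Limitations names confounding and bias and promises control of known confounders. T0 also holds likely correlates of use, such as HbA1c, complications, diabetes duration and comorbidity. These allow a partial check of imbalance, but they are not in the stated adjustment set and do not replace prior use.

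**Stronger readings that the documents do not support:**

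- *That frequent attenders become users.* Information is given in consultations, but all patients are to be offered the service. No passage says that attendance drives uptake, so the direction of bias is unknown.
- *That the bias is about 50%.* That figure would set an invented gap of 0.5 visits against one visit a year. The denominator is not firm either: "Standard care at the outpatient clinic includes a once-a-year consultation with an endocrinologist, a diabetes specialist nurse, or both", and some patients have added consultations.
- *That the planned follow-up-minus-baseline analysis breaks down.* That text concerns scores, and only the primary outcome is expressly defined as a change. Nothing says that visit counts will be analysed this way.
- *That a count for the year before T0 would suffice.* For users it can include exposed time.

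**Source of data.** Health Economy names survey data for resource use, so record-based counts cannot be assumed to be planned already. This adds to the fix but does not remove the point.

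**Conclusion.** The point holds as a design weakness in a secondary outcome and in the economic evaluation. As scheduled, a T1 difference in use or cost between users and nonusers cannot be read as an effect of the digital PROM, because any pre-existing difference in use passes into it undiminished except for what age, gender and education explain.

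The size and direction of the bias cannot be derived from the documents, and the simulated rates rest on assumed inputs. If the groups happened to have equal prior use given those three variables, the comparison would be unbiased; the plan has no means of showing this. The conclusion assumes that Table 3 is complete as to what is collected. The primary outcome, measured at T0 and T1, is not touched.

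**What to change.** 1. During the planned hospital record extraction, also take clinic consultations by type and by profession, non-attendance and late cancellations for a 12-month pre-exposure window. For users this is the 12 months before the recorded app start date. For nonusers it is a matching calendar window, for example from index dates assigned from the distribution of user start dates. Do not use the 12 months before T0 as the baseline for users.
2. Add this window to Table 3.
3. Analyse the follow-up counts in a Poisson or negative binomial model that includes the pre-exposure count and the stated confounders. Because adjustment for one prior-year count can leave part of a stable gap, show a group-by-period comparison beside it as a sensitivity analysis.
4. Report items available only by self-report (GP visits, work absence) as descriptive comparisons, not as effects.
5. State in Health Economy that clinic contacts come from records as well as the survey, and adjust the clinic part of incremental cost in the same way.

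The cost is a slightly longer extraction from records that are already being opened. As the window lies in the past, it can also be done for patients already enrolled. If it is not done, aim 1 should describe the utilization difference rather than claim an effect.

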	**GP^a^ visits**					
		Number of GP consultations			✓	
	**Absence from work**					
		Days of absence			✓	
**Patient involvement**						
	**Patient involvement and shared decision-making**					
		6 items reflecting decision-making, communication, and interaction 5-point Likert scale from 1, “absolutely not” to 5, “to a very high degree,” with an added “I don’t know” Higher scores reflect a higher feeling of involvement	✓		✓	
**Digital user data**						
	**Participation in the digital outpatient care**					
		Yes or no, including start date	✓		✓	
	**PROMs^b^ completed**					
		Type of measures and frequency, number			✓	
	**Messaging services**					
		Frequency of use and number			✓	
	**Use of other mobile health apps**					
		2 items reflecting use and frequency Including open-ended responses	✓		✓	

^a^GP: general practitioner.

^b^PROM: patient-reported outcome measure.

The items reflecting patient involvement [48] and patient role [49] have been previously adapted from their original form and used in the DiabetesFlex study [16,17]. For this project, the items adapted in the DiabetesFlex study have been translated from Danish by the project team into Norwegian and then back-translated by a bilingual Danish researcher not affiliated with the project. The translation was then reviewed by ALJ, AT, and IS, and small adjustments were made before a translation consensus was reached.

#### Health Economy

To estimate the cost-effectiveness of the digital care model, we will conduct a cost-utility analysis based on decision-analytic modeling [50,51]. Those using the digital PROMs will be compared with those continuing with the standard follow-up. Health benefits will be measured using the EQ-5D-5L at baseline and at 12 months. Data for health care resource use will be collected using survey data on general practitioner visits, visits to nurses and other health care professionals, and absences from planned consultations and hospital admissions (Table 3). The time used for training will be based on experiences from implementing the digital care model. Microsimulations will be used to estimate the cost of traveling and other patient expenses. The unit costs will be based on the Norwegian reimbursement systems, the marked prices, and the literature. The results will be reported as incremental cost-effectiveness ratios with credibility intervals and cost-effectiveness acceptability curves. We use probabilistic sensitivity analysis to estimate the uncertainty caused by parameter uncertainty and use deterministic sensitivity analysis to assess the effect of changes in resource use, unit cost, and assumptions [52].

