## Methods

### Study Design

This protocol describes a prospective, multimethod observational cohort study to investigate the relevance and effects of digital and flexible services using PROMs. The PROM in the planned trial is based on DiabetesFlex, which was developed and implemented in Danish health care services for type 1 diabetes [16,17,24], and it has been adapted to a Norwegian digital context in preparation for this study [25]. Consenting participants will be enrolled for 12 months, with assessments at baseline (T0) and 12 months (T1), with additional data from electronic health records, field observations of clinical video, or in-person consultations, along with individual in-depth interviews with the patients and diabetes health care personnel (Figure 1). Field observations and in-depth interviews among the patients participating in the digital PROMs will be conducted at any given time for those not participating in the survey and after completing T1 for those consenting to the survey study to avoid contamination of the survey and interview data.

This study is a collaboration between Akershus University Hospital and Oslo Metropolitan University—OsloMet and will be conducted at the Endocrinological Outpatient Clinic at Akershus University Hospital.

This protocol is reported in line with the Standard Protocol Items: Recommendations for Interventional Trials (SPIRIT) guidance [26]. The reporting of the proposed study and participation in digital tools and PROMs in clinical practice will be guided by better reporting of interventions: template for intervention description and replication (TIDieR) [27] and the PRO reporting guide [28].

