### Procedures

Eligible patients will be identified and given brief information at the outpatient clinic by health care professional staff. If the patients are interested, they will be contacted by a researcher (IS or MAM). If they consent to participate after receiving oral and written information, their written consent will be secured either through Nettskjema digital consent or through a paper-based consent form. Immediately after their consent, the patients can choose whether they will fill out the baseline questionnaire digitally through Nettskjema, paper-based in the mail at home with a free return envelope, or through a telephone interview with a researcher (IS or MAM). For consenting participants not responding to or returning the baseline questionnaire or the 1-year follow-up, an automatic email reminder will be sent, followed by a phone call reminder and a SMS text message reminder if they still do not reply. The digital consents and the digital questionnaire data will be securely stored in the Service for Sensitive Data at the University in Oslo. Paper-based consent forms and questionnaires will be securely locked in a safe for storage, and the paper-based questionnaires will be manually entered into SPSS (IBM Corp). Data from the patients’ medical records will be extracted by a researcher (IS), and 10% of the extractions will be controlled by a second researcher (MAM) to ensure valid and reliable data extraction.

Health care personnel will be recruited for 2 purposes: in-depth interviews and observations of consultations with patients engaged in the digital PROM. The personnel will be recruited from the department, and written informed consent will be secured using the same procedures as those for the patients.

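### Survey data is the only source named for health care use, which implies about a year of recall for clinic visits and missed consultations although the hospital record is already being extracted

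*Protocol article*

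**What the plan says.** All references are to the protocol article.

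- **Role of the data.** Study Outcomes, Overview, lists among the secondary outcomes "health economics, and the use of health service resources". Health care utilization is also part of the first aim, and Health Economy uses it as a cost input.
- **Stated source.** Health Economy says "Data for health care resource use will be collected using survey data on general practitioner visits" and continues the same list with "visits to nurses and other health care professionals, and absences from planned consultations and hospital admissions (Table 3").
- **Items and timing.** In Table 3 the health care use rows include "Number of on-attendance and number of late cancelations" and "Number of consultations with a physician, a nurse, and a nutritionist". There are also rows for consultation type, general practitioner visits and days off work. All five rows are ticked at T1 only. The paragraph that introduces Table 3 names no source.
- **Records.** Study Design describes the two survey assessments "with additional data from electronic health records". Procedures adds "Data from the patients’ medical records will be extracted by a researcher", with a second researcher checking 10%. Where the article says what is extracted, it names clinical variables and MyDignio use (Study Outcomes, Overview) and sociodemographic variables (Sociodemographic and Clinical Variables).

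**The concern.** A patient asked at 12 months how many consultations they had, with which profession, and how many they missed must reconstruct administrative facts. For appointments at the study clinic, the clinic that books and holds them is the natural source. The study runs at that one clinic, and its researchers already open each participant's record.

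The counts matter to the study's argument. The Discussion cites the Danish precursor study as having reduced face-to-face visits, so visit numbers are one of the places where a benefit would be expected to show. Measurement would also be uneven across types of contact: digital contacts are to be extracted from the platform, while conventional visits would be recalled. Finally, a participant who does not return the T1 questionnaire would lose utilization data that the record could still supply.

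**Working it through.** The documents give no visit counts, recall-error figure or unit costs, so there is no figure of the plan's own to reproduce. The check is to set the stated sources beside the items.

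| Item | In the Health Economy survey sentence? | Row in Table 3? | Assigned to the hospital record anywhere? |
|---|---|---|---|
| General practitioner visits | Yes | Yes, T1 | No |
| Visits to nurses and other professionals | Yes | Yes, T1 (by profession) | No |
| Missed consultations | Yes | Yes, T1 | No |
| Late cancellations | Not named | Yes, T1 | No |
| Consultation type (physical, video, telephone) | Not named | Yes, T1 | No |
| Work absence | Not named | Yes, T1 | No |
| Hospital admissions | Mentioned | No row | No |

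Four steps follow.

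1. **Source.** Health Economy is the only section that names a source for resource use, and it says survey. It covers professional visits and missed consultations explicitly. It reaches consultation type and late cancellations only through its pointer to Table 3.
2. **Recall window.** The article does not state one. Assessments are at T0 and T1, enrolment lasts 12 months, and these rows are ticked at T1 only. A survey count covering follow-up therefore implies recall over about 12 months.
3. **Availability of a better source.** The article does not say that the record holds appointment data. The inference rests on the clinic delivering the consultations (A Digital and Flexible Service) and its secretaries handling changes to appointments (Health Care Personnel Participants). It is a strong inference for the clinic's own appointments and none at all for contacts elsewhere.
4. **Internal mismatch.** The Health Economy sentence can be read as counting hospital admissions or as absences from them. Either way it points to Table 3, which has no admissions row.

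Two pieces of arithmetic give scale only:

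- Standard care is a yearly consultation with an endocrinologist, a diabetes nurse or both, with one or more added visits in some situations. On a base of one or two visits, one misreported visit is 1/1 = 100% or 1/2 = 50% of that patient's count. This describes a single patient and is not an estimate of bias in a group mean.
- Results reports 34 nonusers so far. One missing T1 questionnaire removes 1/34 = 2.9% of that group's survey-based utilization data. At the recruitment target of at least 35 it is 1/35 = 2.9%.

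**The case against.** The strongest reply is that the document leaves the source open and does not fix it badly. A T1 tick marks a time point, not a mode of collection: HbA1c and LDL cholesterol carry T1 ticks in Table 2 and are plainly not recalled. Table 3 is not a survey form, since it also holds platform counts such as completed PROMs and messages. The Abstract and Study Design mention health-record data in general terms. The list of professional visits in Health Economy is not limited to the study clinic, and a survey is reasonable for contacts that this hospital's record may not hold. An article also commonly leaves item-by-item sources to the full protocol.

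Much of this stands, and it rules out several stronger readings that a reader might infer:

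- *That record extraction is confined to clinical variables.* The Overview does not say so, and a later section adds sociodemographic variables. Extraction of visit counts is not ruled out.
- *That every health care use item is stated to rest on 12-month recall.* The survey sentence does not name consultation type or late cancellations, and the recall window is inferred.
- *That recall error will differ between users and nonusers.* This is plausible because the groups differ in how they make contact, but nothing in the document shows it.
- *That record data would rescue the cost-utility analysis for T1 non-responders.* They would still lack the T1 EQ-5D-5L. Procedures already plans email, telephone and text reminders.

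The planned deterministic sensitivity analysis on resource use helps explore uncertainty in this input, but it would not correct an error that differed by group.

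The reply does not remove the point, because the one explicit statement of source says survey and covers missed consultations. If records were intended, that sentence is wrong. If they were not, a better source is being passed over. Condensation explains an omitted source, not a stated one.

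**Conclusion.** The point holds as a cheap improvement to how a secondary outcome and a cost input are measured. On its plain reading, the article takes professional visits and missed consultations from a survey at T1, with about 12 months of implied recall. It assigns none of the clinic's own consultation or attendance counts to a hospital record that is already being extracted and checked.

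The conclusion rests on two inferences: that the recall window is about 12 months, and that the record holds the clinic's appointments. It is limited to consultations at the study clinic. Self-report is reasonable for general practitioner visits, contacts elsewhere and work absence. No effect on the between-group difference in utilization or on the incremental cost-effectiveness ratio can be given, in size or in direction. Separately, the reference to Table 3 for hospital admissions does not match the table.

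**What to change.** Amend Health Economy and Table 3 so that each resource-use item has a named source:

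- **Hospital record, all consenting participants, fixed T0-T1 window:** number, type and profession of consultations at the study clinic, non-attendance, and late cancellations. Bring these fields under the existing 10% second-researcher check.
- **Survey at T1:** general practitioner visits, contacts outside the hospital, and work absence, with the recall period stated.
- **Hospital admissions:** add a row with a source, or remove the reference to Table 3.

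If extraction from the record was intended all along, correcting the Health Economy sentence and adding a source column to Table 3 is enough.

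The cost is a few more fields in an extraction already under way, and possibly revised wording in the data-access approval. It can be done retrospectively, with no new visits or patient contact. Participants who do not return T1 would keep their clinic utilization data, but their T1 EQ-5D-5L would remain missing and must still be handled in the cost-utility analysis.
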